### Data monitoring

The data safety monitoring board (DSMB) appointee who will oversee the study is the Osteopathy Professional Experience Learning Co-ordinator in the School of Health and Human Sciences at Southern Cross University. The DSMB appointee will meet with one or more of the principal investigators on a regular basis to review the study data. As this trial includes the administration of manual therapy by supervised interns, the meetings with the DSMB appointee will focus on safety by reviewing adverse event (AE) data as it is collected during the trial. While severe or unexpected AEs are reported to the relevant Ethics Committee (Institutional Review Board) as a matter of standard procedure in any clinical trial, the DSMB meetings in this trial will track the rate of expected AEs, i.e. the mild to moderate AEs, as a way of monitoring whether participants are being placed at ‘additional’ risk by being treated by interns.

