**Methods:**

The study design is a randomised controlled trial of 372 people with no history of respiratory disease between the ages of 50 and 65 years. The cohort will be divided into three equal groups. The first group will receive a simple 10-min treadmill walking program (Ex). The second group will receive joint mobilisation (MB) of the thoracic spine and ribs plus the same walking program (MB + Ex). The third group will receive joint manipulation (MT) of the thoracic spine and ribs plus the same walking program (MT + Ex). All interventions will be administered a total of six times over a 3-week period. The primary outcome measure is lung function: forced expiratory volume in the 1st second and forced vital capacity. The secondary outcome measures include chest wall expansion (tape measurements) and quality of life measurements (36-Item Short Form Health Survey). Outcome measurements will be taken by blinded assessors on four occasions over a 9-week period. Adverse event data will be gathered at the beginning of each intervention session.

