## Methods/design

### Study design

The trial is designed as a randomised controlled trial and fulfils the requirements of the Standard Protocol Items: Recommendations for Interventional Trials (SPIRIT) checklist [12] (Additional file 1). The trial will evaluate 372 participants randomly allocated to three equal groups. Participants in Group 1 (Ex), the active control, will undertake a simple exercise program involving a standardised 10-min walking program performed on a treadmill. Participants in Group 2 (MB + Ex) will have manual therapy in the form of joint mobilisation (MB) administered to their thoracic spine and ribs prior to performing the same exercise regime as Group 1. Mobilisation consists of a pre-determined series of manoeuvres (mobilisation protocol) designed to increase joint mobility in the thoracic spine and rib cage (Grade III–IV mobilisation as per Maitland [13]). Participants in Group 3 (MT + Ex) will have manual therapy in the form of joint manipulation (manipulation protocol) administered to their thoracic spine and ribs prior to performing the same exercise regime as Group 1. Manipulation (MT) consists of two separate manipulations (Grade V mobilisation as per Maitland [13]), each involving a high velocity low amplitude (HVLA) thrust directed at the inter-vertebral, costo-vertebral and costo-transverse joints. The first manipulation will be delivered at the level of the upper/middle thoracic spine, while the second will be at the level of the middle/lower thoracic spine. Two different manipulation techniques are available under the trial’s manipulation protocol: supine and sitting. The supine technique, referred to as the ‘Opposite-side thenar/transverse drop’ [14] or ‘Supine wing’ [15] technique, can be delivered with the participant’s thoracic spine in flexion or extension. The sitting technique, referred to as a ‘Long-axis distraction’ [14] or ‘Sitting winglift’ [15] technique, can be delivered using an axilla or elbow hold. The choice of technique will be determined by the treating clinician based on biomechanical factors such as the patient-to-practitioner size ratio. All MT intervention will be administered as non-specific, multi-joint (group) manipulations. Administering MT in this way reduces the total number of manipulations required to address the thoracic spine within a single intervention session, as each manipulation has the potential to affect several thoracic vertebrae and their associated ribs simultaneously. All Ex will be performed immediately after MB and MT intervention, as this has been shown to enhance the synergistic effect of combining the two interventions [9, 16–18]. All intervention sessions will last between 15 and 20 min.

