**Fig. 2 Fig2:**
[figure not shown]
SPIRIT figure showing times points for enrolment, interventions and assessments. *Ex* exercise, *MB* mobilisation, *MT* manipulation, *FEV*_*1*_ forced expiratory volume in the 1st second, *FVC* forced vital capacity, *SF-36* 36-Item Short Form Health Survey

All MB and MT will be administered by students enrolled in the Masters of Osteopathic Medicine program at Southern Cross University who have been trained in the relevant manual therapy techniques used in this trial. They will be under supervision at all times by a registered osteopath.

A manipulation will be deemed successful by the presence of an audible release. All releases will be recorded on the participant’s file by the treating intern as either ‘absent’ (0), ‘single’ (1), or ‘multiple’ (2) for each manipulation. Should a deviation from the intervention protocol occur, the supervisor will be on hand to either approve the deviation or ensure a return to protocol. Any protocol violations, whether for clinical or non-clinical reasons, will be recorded on the participant’s file by the treating intern at each intervention session.

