### Adverse events

The risks of harm or discomfort to participants in this project primarily relate to the potential for AEs resulting from MT intervention. The majority of reported AEs associated with these interventions are mild (muscle soreness and local discomfort), self-limiting, require no further medical attention and resolve within 48 h [19]. Moderate AEs, such as fracture, have also been reported following spinal manipulation and have been estimated to occur at a rate of 1 in 40,000 [20]. Reports of major or catastrophic AEs resulting from spinal manipulation have appeared in the literature with nearly all associated with neck (cervical) manipulation. This trial involves manipulation of the thoracic spine and ribs only and does not include any neck manipulation. The MT techniques used in this trial are similar to the ones used in three previous studies on people with chronic obstructive pulmonary disease (COPD) [16, 17, 21]. There were no major or moderate AEs reported in those studies. Mild AEs associated with MT intervention were reported at a rate of 15% (18 out of 112) in the study on patients with moderate COPD (average age 56.1 years) [16], at a rate of less than 1% (2 out of 403) in the study on patients with moderate to severe COPD (average age 65.5 years) [17] and at a rate of 29% (21 out of 72) in the case series on patients with moderate to severe COPD (average age 79.1 years) [21]. As the trial reported here is being conducted on healthy participants with no history of respiratory disease, it is reasonable to predict that the risk of harm or discomfort to participants will be less than that in the previous studies on people of a similar age with respiratory disease. However, as this trial includes the administration of manual therapy by clinicians with limited clinical experience (interns), we have used an incident rate of 41% for mild AEs, taken from Carnes et al. [19], as the threshold for triggering an automatic halt to the study.

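### Tracking the adverse event rate cannot show whether interns add risk, because interns give all the manual therapy; restate the aim and review events by arm

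*Protocol article*

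**What the plan says.** All places are in the Protocol article.

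- **Data monitoring.** The stated purpose is to learn whether anyone is "being placed at ‘additional’ risk by being treated by interns". To that end, the safety appointee's meetings "will track the rate of expected AEs, i.e. the mild to moderate AEs, as a way of monitoring whether participants" face such a risk. No comparison group is named.
- **Protocol description.** "All MB and MT will be administered by students enrolled in the Masters of Osteopathic Medicine program", under constant supervision by a registered osteopath.
- **Study design.** Participants in the exercise arm "will undertake a simple exercise program involving a standardised 10-min walking program performed on a treadmill". The two manual therapy arms do the same walk after their treatment.
- **Abstract, Methods.** All interventions are given six times over three weeks, and "Adverse event data will be gathered at the beginning of each intervention session". This is not limited to the manual therapy arms.
- **Adverse events.** Mild event rates are cited from three earlier studies in COPD: "15% (18 out of 112"), "less than 1% (2 out of 403") and 29% (21 of 72). The authors expect a lower risk here because participants are healthy. They also take a mild event rate of 41% from a further source as the trigger for an automatic halt, and give the interns' limited experience as the reason.

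**The concern.** Additional risk from interns is a contrast: the event rate when interns treat, minus the rate when experienced clinicians give the same treatment to similar people. The section names only the first term. The trial cannot supply the second, since no participant has manual therapy from anyone but a student. The reference must therefore come from outside, and the outside rates differ too much, and come from too different a population, to serve as one.

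A monitor following the section as written could read a given rate as reassuring or as alarming, depending on which earlier study is taken as the standard. A single tracked rate also mixes events caused by manual therapy with events from walking and from repeated questioning. The section makes this tracking the focus of the safety meetings, and recruitment was ongoing at submission, so a correction can still take effect.

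**Working it through.** **1. The quoted rates (Adverse events section).**

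- 18/112 = 16.1% (printed as 15%, a small slip); exact 95% CI 9.8% to 24.2%
- 2/403 = 0.50%; exact 95% CI 0.06% to 1.8%
- 21/72 = 29.2%; exact 95% CI 19.0% to 41.1%
- 41%: no counts given, so it cannot be recomputed

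Span across the three studies: 0.2917 / 0.00496 = 58.8. If the 41% ceiling is counted as well: 0.41 / 0.00496 = 82.6. The first figure is the fair one, because 41% is an action threshold and not one of the three study rates. The article does not say whether the counts are per participant or per session. If 2/403 were per session (assumption) with six independent sessions, it would become 1 − (1 − 0.00496)^6 = 2.9% per participant, and the span to 29.2% would fall to about 10-fold (0.292 / 0.029).

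**2. Why the intern effect is not identified.** Suppose the manipulation arm shows 30% and the exercise arm 5% (both assumed). The arm difference is 25 points whatever the operator effect. The excess due to interns is 30% minus the unknown rate under experienced clinicians:

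| Experienced-clinician rate (assumed) | Excess due to interns |
|---|---|
| 0.5% | +29.5 points |
| 16% | +14 points |
| 29% | +1 point |
| 41% | −11 points |

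The same trial data fit a large harm, no effect or a benefit.

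**3. Whether the 41% ceiling fills the gap.** Assume the rate is per participant within one arm of 124. Reaching 41% needs 51 or more participants with an event (0.41 × 124 = 50.8). The binomial probability of this is below 0.0001 at a true rate of 16%, 0.003 at 29% and 0.52 at 41%. A rise from 16% to 29% would almost never reach the ceiling. It acts as an absolute limit and does not measure extra risk.

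**4. What the exercise arm can give.** With n per arm, SE = √[p₁(1 − p₁)/n + p₂(1 − p₂)/n], half-width = 1.96 × SE, and power (two-sided 0.05, normal approximation) = Φ(|p₁ − p₂|/SE − 1.96). The article gives no exercise-arm event rate, so the rates are assumed.

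| Rates | n per arm | SE | 95% half-width | Power |
|---|---|---|---|---|
| 16% v 5% | 124 | 0.0383 | 7.5 points | 82% |
| 16% v 5% | 62 | 0.0542 | 10.6 points | 53% |
| 16% v 5% | 31 | 0.0766 | 15.0 points | 30% |
| 30% v 15% | 124 | 0.0522 | 10.2 points | 82% |

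At 124 per arm and 80% power, the detectable manual therapy rate is about 10.7%, 15.9%, 23.2% or 35.9% for exercise-arm rates of 2%, 5%, 10% or 20%. The contrast is informative at full enrolment and weak early on.

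**The case against.** The strongest reply is that the article does state a comparator. The 41% ceiling is tied to an action and was set with the interns in mind, while the three COPD rates are background. That is a fair reading, and it would be wrong to say that the rate is tracked against nothing. But a ceiling above every quoted study rate limits total harm; it cannot say whether interns raise the rate.

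A second reply is that layouts of safety tables belong in a monitoring charter or the full protocol. This also stands. A reader might infer that the plan rules out review by arm, or leaves the trial unable to set harm against benefit at the end. The article supports neither: it is silent on review by arm, and events are gathered from participants whose allocation is recorded, so a final comparison remains possible. The point rests on the stated purpose, which no table layout could rescue.

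A reader might also infer that the exercise arm is a ready-made reference for the intern question. It is not. That arm has no manual therapy, so the contrast combines technique and operator.

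Finally, repeated intervals at small numbers invite over-reaction. This is right, and it is why the differences should be descriptive, with no action rule attached.

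**Conclusion.** The stated purpose in Data monitoring cannot be met by this design, since students give all the manual therapy and the three external study rates span 59-fold in a different population. This conclusion needs no assumption about event rates. The width of the span depends on unstated denominators (about 10-fold if the lowest rate is per session), but even that is too wide for a benchmark.

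What can be measured is the excess of intern-delivered manual therapy over walking alone. Its precision, about ±7.5 points at 124 per arm, rests on assumed rates of 16% and 5% and on events being asked about in the same way in all three arms, as the abstract suggests. The point touches no efficacy estimate. It should be corrected because safety oversight relies on the claim and could draw false reassurance from it.

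**What to change.** In Data monitoring, replace the sentence on tracking expected events with wording such as:

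> At each meeting the safety appointee will review the cumulative proportion of participants with any adverse event in each arm, with the differences MB + Ex minus Ex and MT + Ex minus Ex and their 95% confidence intervals. These are descriptive. They estimate the risk of intern-delivered manual therapy over walking alone and do not isolate risk due to interns. The same differences will be reported at the end of the trial.

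This also fixes the denominator as participants for these tables. The halt rule in Adverse events is outside this change.

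Cost: one table per meeting from data already collected, plus the wording. There are two small downsides. Precision is low early in the trial, and tables by arm must be kept from the blinded outcome assessors.

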### Adverse events

The risks of harm or discomfort to participants in this project primarily relate to the potential for AEs resulting from MT intervention. The majority of reported AEs associated with these interventions are mild (muscle soreness and local discomfort), self-limiting, require no further medical attention and resolve within 48 h [19]. Moderate AEs, such as fracture, have also been reported following spinal manipulation and have been estimated to occur at a rate of 1 in 40,000 [20]. Reports of major or catastrophic AEs resulting from spinal manipulation have appeared in the literature with nearly all associated with neck (cervical) manipulation. This trial involves manipulation of the thoracic spine and ribs only and does not include any neck manipulation. The MT techniques used in this trial are similar to the ones used in three previous studies on people with chronic obstructive pulmonary disease (COPD) [16, 17, 21]. There were no major or moderate AEs reported in those studies. Mild AEs associated with MT intervention were reported at a rate of 15% (18 out of 112) in the study on patients with moderate COPD (average age 56.1 years) [16], at a rate of less than 1% (2 out of 403) in the study on patients with moderate to severe COPD (average age 65.5 years) [17] and at a rate of 29% (21 out of 72) in the case series on patients with moderate to severe COPD (average age 79.1 years) [21]. As the trial reported here is being conducted on healthy participants with no history of respiratory disease, it is reasonable to predict that the risk of harm or discomfort to participants will be less than that in the previous studies on people of a similar age with respiratory disease. However, as this trial includes the administration of manual therapy by clinicians with limited clinical experience (interns), we have used an incident rate of 41% for mild AEs, taken from Carnes et al. [19], as the threshold for triggering an automatic halt to the study.

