### Protocol description

Volunteers who meet the inclusion criteria will be given an information sheet and asked to provide written consent to participate in the trial. They will then undergo a physical examination screening for the presence of other contra-indications to thoracic MB or MT such as thoracic spine surgery or recent trauma followed by an information session designed to familiarise them with the use of a treadmill. After a volunteer has successfully completed these tasks, baseline measurements will be taken. These include age, height, weight, blood pressure, heart rate, lung function assessment (spirometry), chest wall expansion (tape measure) and quality of life scores (SF-36). A participant is then enrolled in the trial, given a trial-specific identification (ID) number and allocated to a group on a sequential basis using a computer-generated random sequence list drawn up prior to the start of the trial by a person not involved in any other aspect of the trial. Participants will be directed to not reveal their group allocation to the blinded assessor during assessment. The study protocol flow of participants is outlined in Fig. 1.

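### Read together, the Adverse events and Data monitoring sections place fracture in the rate-tracked class of expected AEs, although the article's own evidence shows a fracture would be unexpected

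*Protocol article*

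**What the plan says.** Two neighbouring sections of the protocol article bear on this.

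- **Adverse events** uses the labels mild, moderate, and major or catastrophic. Mild events are illustrated by soreness and discomfort that settle within two days without treatment. For the next class it says "Moderate AEs, such as fracture, have also been reported following spinal manipulation", with a rate of 1 in 40,000. Of three earlier COPD studies with similar techniques it says "There were no major or moderate AEs reported in those studies". It sets one stopping rule: "we have used an incident rate of 41% for mild AEs", "as the threshold for triggering an automatic halt to the study".
- **Data monitoring** deals with routing. One sentence opens "While severe or unexpected AEs are reported to the relevant Ethics Committee", describes this as standard trial procedure, and goes on to say that the DSMB meetings will "track the rate of expected AEs, i.e. the mild to moderate AEs". The stated purpose is to see whether treatment by interns puts participants at additional risk.

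Other safeguards are in place. The abstract says "Adverse event data will be gathered at the beginning of each intervention session". The Protocol description section provides for "physical examination screening for the presence of other contra-indications to thoracic MB or MT" and for constant supervision by a registered osteopath. Participant characteristics excludes people with diagnosed osteoporosis. The DSMB appointee reviews AE data as they come in.

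**The concern.** In Data monitoring, *expected* is defined by severity class rather than by how likely an event is. Because Adverse events calls fracture moderate, the definition carries fracture into the expected class along with muscle soreness. Expected events are followed as a rate; only severe or unexpected ones are named for the ethics committee.

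Following a rate suits a common, minor event. It does not suit a rare and serious one, where each case should be looked at individually. Fracture is a relevant harm here: participants are 50 to 65, the Background lists osteoporosis among normal age-related changes of the thoracic spine and chest wall, only diagnosed osteoporosis is excluded, and students deliver high-velocity thrusts. At stake is whether the written rule leads staff to report and review a fracture promptly, or leaves them to decide that the article's label should not apply.

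**Working it through.** **Step 1: the labels side by side.**

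| Question | Where answered | Answer for fracture |
|---|---|---|
| Which severity class? | Adverse events | Moderate |
| Is that class expected? | Data monitoring | Yes: mild and moderate are both called expected |
| Which AEs are named for the ethics committee? | Data monitoring | Severe or unexpected; as labelled, fracture is neither |
| What handling is stated for expected AEs? | Data monitoring | Rate tracking at DSMB meetings, within general review of AE data |

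No other section of the article gives a rule for fractures or defines a serious AE.

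**Step 2: is the expected label consistent with the article's own rate?** The article gives no expected count for this trial, so there is no figure to reproduce. Inputs:

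- 124 participants per arm (Sample size calculation)
- six sessions each (abstract)
- two manipulations per session in the manipulation arm (Study design)
- a rate of 1 in 40,000 (Adverse events), whose unit is not stated, so three units are tried as an assumption.

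Sessions: 124 × 6 = 744. Manipulations: 744 × 2 = 1,488.

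Expected count = m / 40,000. Chance of at least one = 1 − (1 − 1/40,000)^m.

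| Assumed unit | m | Expected count | Chance of at least one |
|---|---|---|---|
| Participant | 124 | 0.0031 | 0.3% |
| Session | 744 | 0.0186 | 1.8% |
| Manipulation | 1,488 | 0.0372 | 3.7% |

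On every reading the most likely number is zero. As written, the rate covers moderate AEs with fracture as the example, so the whole class is this rare.

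**Step 3: the earlier studies.** The mild-AE denominators are 112, 403 and 72, which sum to 587. If these also apply to moderate AEs and can be pooled (both are assumptions; their units are not stated), zero events give a one-sided 95% upper limit of 1 − 0.05^(1/587) = 0.51%. For the manipulation arm that is at most 124 × 0.00509 = 0.6 events if the limit is per participant, or 744 × 0.00509 = 3.8 if per session. This is a rough ceiling, useful only for judging the workload of individual review.

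**The case against.** The strongest reply is that the two sections do not share one grading scale. The fracture sentence summarises published harms and is not presented as the trial's grading rule; *severe* is not a grade in Adverse events at all. Unexpected AEs have their own route to the ethics committee, and in the ordinary sense of the word a fracture at 1 in 40,000 is unexpected. Ethics reporting is said to follow standard procedure, whose definitions may sit in the full protocol. Much of this stands, and it limits the point to inconsistent wording. It does not remove the point: Data monitoring says outright which classes are expected, and moderate is one of them.

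Three stronger readings are tempting, and the article does not support them:

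- *A fracture would go unreported.* Staff could grade it severe, or treat it as unexpected, and the DSMB appointee sees AE data as collected.
- *The 41% halt is faulty because fractures do not count towards it.* A threshold on mild AEs is meant for common soreness. That it does not count fractures is not an error.
- *One fracture would be lost in a pooled rate.* The article does not say that mild and moderate AEs are pooled. A separate moderate count that moved from zero to one would be obvious.

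**Conclusion.** The point holds as an inconsistency in what the article states. Its labels, read together, put fracture among the expected, rate-tracked AEs, while its own evidence makes fracture an event that should not be expected: a 0.3% to 3.7% chance of any in the manipulation arm, and no moderate or major AE in the three earlier studies.

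The range assumes that the quoted rate carries over to this trial and depends on the unit chosen. The rate is not stated to apply to supervised interns, so the true chance could differ. No estimate, power figure or efficacy conclusion is affected. The absolute risk is small, but the matter concerns participant safety and the correction is cheap, so it is worth making.

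**What to change.** 1. In Data monitoring, limit expected AEs to the mild ones as Adverse events already describes them: muscle soreness and local discomfort that are self-limiting, need no medical attention and are gone within 48 hours.
2. Add that any fracture, or any other AE after mobilisation or manipulation that needs medical attention, is treated as unexpected, reported promptly to the ethics committee, and reviewed individually by the DSMB appointee. Using the need for medical attention as the trigger avoids relying on a moderate grade that the article illustrates only by fracture.
3. Leave the 41% halt for mild AEs unchanged.

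The cost is a few sentences and a short ethics amendment; Trial status says recruitment was still open at submission. Case reviews should be rare: a fracture review would arise with a probability of 0.3% to 3.7% in the manipulation arm at the quoted rate. Reviews of other AEs needing medical attention, and any in the mobilisation arm, come on top and cannot be sized closely from the article.
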